# Resources

This contributes to a Metro North Clinician Research Fellowship awarded to A/[name] to improve recovery outcomes after an admission to the intensive care unit (ICU). He is able to provide his input to the intervention as an in-kind contribution.

The study will be conducted in the Redcliffe Post Intensive Care Clinic, with representatives from Intensive Care, Psychiatry, and Allied Health in the investigative team. The study will be operating on the in-kind contributions from the investigators, and existing infrastructure already established in the clinic. The study team brings the complementary expertise and authority needed to deliver the study.

# Background and rationale

Clinical research and technological innovation have greatly improved survival after ICU admission such that around 90% of those admitted to ICUs are discharged alive [1]. As a result of this, there has been a shift in outcome focus from survival to quality of life after survival. Evidence demonstrates that recovery is often complicated and partial [2], with up to 80% of people discharged from the ICU (ICU survivors) experiencing various physical, cognitive, and/or psychological complications and enduring impairment which can persist up to 15 years after discharge [3-5]. These various impairments, occurring separately or in combination following an ICU admission are termed ‘post intensive care syndrome’ (PICS).

A recent concept analysis of PICS defined its attributes as new or worsening multidimensional impairments, physical dysfunction, psychological disorder, cognitive impairment, failed social reconstruction or impaired multidimensional symptoms which persist beyond ICU and hospital discharge[6].

Mental illness is a common feature of PICS. A large cohort study of 4,943 ICU survivors in the UK found the prevalence of anxiety, depression, and PTSD to be 46%, 40% and 22% respectively, with 18% meeting criteria for all three conditions [7]. A recent study also found an increased prevalence of mental illness treatment and psychotropic medication use in the 5 years following an ICU admission when compared to the 5 years prior [8].

The prevalence and burden of PICS remains under described in Australia [9], and may vary between ICU populations, but available data demonstrate that it is associated with substantial personal and ﬁnancial burden for patients and families[10]. Disrupting social engagement and employment, health and social costs are immense [3, 11, 12]. Specifically, an association has been found between post-ICU psychological morbidity and poor quality of life (QoL) across all domains regardless of aetiology[13].

With the current evidence base for PICS being scarce internationally, and available evidence demonstrating that current interventions are not effective longer-term; further research into prevention, early diagnosis and intervention of this syndrome is considered internationally as a priority [14]. Many post-ICU clinics review patients sometime after discharge, but to our knowledge the effect of an early psychiatric intervention soon after ICU discharge on PICS outcomes has not been investigated. This is despite a recent meta-analysis demonstrating benefit from early psychological intervention targeted to symptomatic individuals following recent trauma[15] and a recent overview of PICS emphasising the importance of early screening and treatment of psychological morbidity to prevent longer term psychological impairment, and suggesting that future research in post-ICU clinics needs to find ways for a more targeted approach to intervention delivery[16].

We hypothesise that an early psychiatric intervention involving evaluation, initial treatment (such as psychoeducation and pharmacotherapy), and referral is feasible and practicable to implement in a post-ICU clinic and acceptable to that patient population Such an intervention may contribute to an improved sense of self-efficacy, improved access of ongoing therapy, and a subsequent reduction in the long-term burden of PICS – both for the individual patients needing this care, and on broader health systems.

# Aims and objectives

The primary objective of this pilot RCT study is to:

1. To evaluate feasibility (cost and practicability) and acceptability of an early psychiatric intervention in a post-ICU clinic.

Secondary Objectives are:

1. Assess the impact of early psychiatric assessment and provision of referral options on self-efficacy and rates of health service access for patients requiring psychological intervention post-ICU
2. Measure the change in symptom severity for anxiety, depression, and PTSD between presentation, and 6 months after presentation.
3. Measure the impact on work, income, and independence in activities of daily living (ADL)

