## Sampling and recruitment

Patients attending the Redcliffe Post-ICU clinic will be informed about the trial of an inclusion of an early psychiatric review as part of the clinic following their completion of standard clinic cares (see Appendix 1 for the Standard Operating Procedures).

If the patient expresses interest in the study, they will be provided written and verbal information regarding the purpose and aims of the study and invited to ask any questions they have about the study before being invited to participate. Potential participants will not be aware if they have been randomised to the control or intervention arm at this stage.

The potential participant will be provided multiple opportunities to discuss the study with members of staff not involved in the study. Information will be provided in writing and verbally before the patient is invited to consent to participate in the study.

A patient information and consent form will be provided. People who agree to participate will complete the written consent form before any data collection takes place. Patients who consent to participate will be randomised using a simple randomisation schedule. Participants randomised to the intervention arm will be offered an appointment with the psychiatrist in addition to standard clinic cares, whereas participants randomised to the control arm will receive standard clinic cares only.

For those attending their appointment over the phone, verbal consent will be obtained and witnessed. People who give consent will give permission for research staff to access data from their clinical records and will complete a series of questionnaires examining their premorbid function, experiences in ICU and their subsequent recovery across a range of domains.

To monitor recruitment, a re-identifiable log will be kept that will document patients eligible for approach, and subsequent contact.

Participants will be able to withdraw from the study at any time. If a participant that has been randomised to receive the early psychiatric intervention chooses to withdraw consent, they will receive the standard cares provided by the clinic without the intervention, and any collected data will be withdrawn from the study.

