## Post Appointment Questionnaire

To address the primary outcome, the **Post Appointment Questionnaire** is an 8 item self-reported acceptability measure that has been specifically developed for this study. It has been adapted from similar surveys used in previous acceptability studies. Questions focus on whether the participant found their appointment helpful, how confident they feel about managing any psychological symptoms they have or may develop, and how optimistic they feel about their recovery.

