## Follow-up Survey

At the 6-month timepoint, participants will repeat the Post Appointment Questionnaire, PICS Measures (including HADS and EQ5D-5L), Life Events Checklist, Generalised Self Efficacy Screen and Patient Employment Information Questionnaire, as well as the Health Services Use Questionnaire described below. The follow-up Survey can be found in Appendix 3.

This **Health Services Use** Questionnaire has 11-items and been adapted from a questionnaire utilised in a recent injury vulnerability study[26]. It explores how often the participant has attended a range of clinical, allied health and alternative health services, whether these services were helpful for their mental health, and for those think they needed more help from health professionals than was accessed, the main reason they didn’t get this help.

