## Statistical analysis

The demographics and results of the Baseline Outcome Measures Bundle will be described using proportions and associated 95% confidence intervals and compared between intervention and control groups to check the integrity of the randomisation.

Responses to the Post Appointment Questionnaire will be assumed to be additive and averaged to produce the primary outcome measure. Differences between groups will be assessed using t-test.

Changes in secondary outcome measures between baseline and 6 months will be compared between intervention and control groups to identify any clinically and statistically significant differences using ANCOVA regression with patients results at baseline fitted as a covariate. The model residuals will be checked to look for outliers and bi-modality. Leave-one-out sensitivity analyses will be used to look for patients that strongly influence the results.

Two-by-two tables will be created of the predicted and observed PICS, together with statistics on sensitivity, specificity, and negative and positive predictive value. Models will be checked for influential observations and outliers. The results will be reported using the EQUATOR TRIPOD checklist to ensure completeness and transparency[29].

The overall characteristics of the sample will be described using summary statistics. This will help inform the generalisability of our results. The number of patients approached and consented will be tabulated, together with the number who dropped out or died.

.

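### Feasibility, including cost, is in the primary objective, but the only primary outcome measures acceptability and nothing described records psychiatrist time or intervention cost

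*Protocol*

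**What the plan says.** The Aims and objectives section gives one primary objective: "To evaluate feasibility (cost and practicability) and acceptability of an early psychiatric intervention in a post-ICU clinic". Feasibility comes first and the protocol itself spells it out as cost and practicability. The Background and rationale section hypothesises that the intervention "is feasible and practicable to implement in a post-ICU clinic and acceptable to that patient population".

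The outcome side is narrower. The Post Appointment Questionnaire section introduces that instrument as the means of addressing the primary outcome and says it "is an 8 item self-reported acceptability measure that has been specifically developed for this study". Its content is whether the appointment helped, confidence in managing symptoms, and optimism about recovery. The Statistical analysis section then states: "Responses to the Post Appointment Questionnaire will be assumed to be additive and averaged to produce the primary outcome measure". The arms are compared by t-test, and no other primary outcome is named.

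Four other statements bear on feasibility:

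- Sampling and recruitment: "To monitor recruitment, a re-identifiable log will be kept that will document patients eligible for approach, and subsequent contact".
- Statistical analysis: "The number of patients approached and consented will be tabulated, together with the number who dropped out or died".
- Follow-up Survey, on the Health Services Use Questionnaire: "It explores how often the participant has attended a range of clinical, allied health and alternative health services".
- Resources: "The study will be operating on the in-kind contributions from the investigators, and existing infrastructure already established in the clinic".

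**The concern.** An objective is answered only if some outcome corresponds to it. Here the first-named part of the primary objective has no designated outcome, and within it the cost component has no described source of data on what the intervention takes to deliver. Because the psychiatrist's input is donated, no payment record will show it either.

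This matters for the use the protocol foresees. The Setting section expects the findings to inform post-ICU care locally and nationally, with new clinics planned in several states. Planners of such clinics would want to know how much psychiatrist time the service needs and how often its components were delivered. Without those data, a statement that the service is feasible would rest mainly on a questionnaire average and on recruitment counts.

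**Working it through.** This is a question of alignment, so the main check is a trace of each part of the primary objective through every data source the protocol describes: the ICU information bundle, the initial survey, the Post Appointment Questionnaire, the follow-up survey, the records request in Study procedure, the recruitment log and the Statistical analysis section.

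| Part of primary objective | Data described | Designated outcome | Analysis stated |
|---|---|---|---|
| Acceptability | Post Appointment Questionnaire, 8 items | Yes, primary | Item average, t-test |
| Practicability: recruitment and retention | Log of eligible and contacted; counts approached, consented, dropped out, died | No | Tabulation |
| Practicability: delivery (psychiatrist seen, treatment or referral initiated, 4-6 week contact) | No dedicated item; clinical steps that should leave a record | No | None |
| Cost: psychiatrist time, cost of delivery | None | No | None |
| Cost: later service use | Health Services Use Questionnaire at 6 months, both arms | No (serves secondary objective 1) | No costing stated |

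Two sources could be mistaken for cost data. The employment questionnaire covers changes in the patient's work and income and serves secondary objective 3. It says nothing about the cost of the service. The records request in Study procedure goes to ICU data collectors and hospital coders, and its list concerns medical history and the hospital admission. It does not list what was done at the psychiatric appointment or how long that took.

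The plan's own figure is the sample of about 30, that is 15 + 15. No derivation is given, so there is nothing to reproduce, and the point does not depend on it.

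The remaining question is whether delivery outcomes would be worth reporting at this size. The exact (Clopper-Pearson) 95% interval for x of n runs from the 2.5% quantile of Beta(x, n - x + 1) to the 97.5% quantile of Beta(x + 1, n - x), with the upper limit set to 1 when x = n. The counts below are assumptions chosen to show precision:

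- Psychiatrist seen, 12/15 = 80%: 52% to 96%.
- Psychiatrist seen, 14/15 = 93%: 68% to 99.8%.
- Psychiatrist seen, 15/15 = 100%: 78% to 100%.
- Retention, 24/30 = 80%: 61% to 92%.
- Retention, 27/30 = 90%: 73% to 98%.

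These intervals are wide, but they can separate near-complete delivery from delivery in about half of patients. That is adequate for descriptive reporting in a pilot.

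For cost, the protocol gives no time per patient. Purely as an assumption, 1.5 to 3 hours per patient over the roughly 80 patients the clinic reviews each year would be 80 x 1.5 = 120 to 80 x 3 = 240 psychiatrist hours. This overstates need at any given time per patient, because patients whose existing illness is already managed receive no further intervention and follow-up applies only where an intervention was initiated. The illustration shows only that, without a time record, the trial could not say where in such a range the service lies.

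**The case against.** A reader might infer that no cost or delivery data are collected at all, and that half of the primary question therefore cannot be answered. The documents do not support that. Recruitment and retention are ordinary feasibility data in a pilot trial, and the protocol both logs and tabulates them. Health service use is collected in both arms. It is a resource-use input to cost and gives at least indirect evidence on whether referrals were taken up. Participants give permission for access to their clinical records. Attendance with the psychiatrist, letters to the GP and the 4-6 week contact are therefore probably recoverable, although none is named as an outcome.

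It is also fair to say that feasibility thresholds, unit costs and the costing method are commonly left to a statistical analysis plan, which is not shown here. One primary outcome with descriptive feasibility reporting is a defensible layout for a pilot. The appendices holding the clinic procedure and the survey items are not shown, so individual items could not be checked.

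These arguments narrow the point but leave its core. The protocol's own descriptions of the surveys mention no intervention-cost item. Psychiatrist minutes are not a routine record: a fixed clinic day and scheduled attendance bound them only loosely, and the preparation, letters and follow-up contact need not fall within the appointment. An analysis plan can decide how to value time, but it cannot supply time that was never logged.

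**Conclusion.** The point holds in limited form and should be fixed. The primary objective includes feasibility, defined as cost and practicability, while the sole designated primary outcome is an acceptability score. Of the two feasibility components, practicability can be partly described from recruitment, dropout and service-use data, with delivery of the intervention probably recoverable but undesignated. The cost of delivering the intervention has no described data source, so that part of the objective cannot be answered as the protocol stands.

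The acceptability comparison is unaffected, and no safety question arises. The conclusion assumes that the unseen appendices match the protocol's descriptions of them. It does not depend on the illustrative hours or delivery counts above.

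**What to change.** In Aims and objectives, Post Appointment Questionnaire and Statistical analysis, name feasibility outcomes beside acceptability and report them descriptively with 95% confidence intervals where they are proportions:

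- patients enrolled, of those eligible and approached;
- patients who saw the psychiatrist, of all those randomised to the intervention arm;
- 4-6 week contacts completed, of patients in whom an intervention was initiated;
- referrals sent.

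For cost, add a one-line log per intervention patient giving psychiatrist minutes for preparation, appointment, letters and follow-up. Value these minutes at a salary rate even though the time is donated. Use the Health Services Use counts already collected as a further resource-use input. Thresholds for what counts as feasible, and the unit costs, can be set in the analysis plan.

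If cost will not be measured, delete the word from the primary objective.

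The change needs a wording amendment and a few minutes of logging for each of about 15 patients. It needs no extra participants, visits or staff, and it alters no part of clinical care. The log has to start with the first intervention patient, because time spent cannot be reliably reconstructed later.

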# Setting

This study will be conducted in the Redcliffe Post Intensive Care Clinic. Redcliffe Hospital is a busy metropolitan hospital in Brisbane, Queensland. The Redcliffe Hospital ICU has 10 beds and admits 500 patients per year. It provides general intensive care management for a broad spectrum of critical illnesses, apart from tertiary cardiothoracic, neurosurgical, trauma and burns management.

Redcliffe Hospital has an established ICU follow-up clinic, where ICU survivors are reviewed around three months after discharge from hospital and extensive data is collected on outcomes from critical illness. Patients are referred to the post-ICU clinic predominantly from the Redcliffe Hospital ICU, but also at times from other local hospital ICUs.

The clinic operates every Wednesday from 0800 to 1600 and reviews around 80 patients per year. The clinician is responsible for making initial contact with patients recently discharged from Intensive Care who meet engagement criteria (ICU admission over 48 hours and no cognitive impairment that prevents participation).  This occurs by phone within the first 1 to 3 months from discharge as a brief encounter to engage with the service. The administrative officer prepares a list of patients to be contacted.

The Redcliffe post-ICU clinic provides an ideal opportunity for this pilot RCT, as it is one of very few post-ICU clinics currently operating in Australia, with processes for data collection and follow-up embedded into standard practice. There has also been growing interest in post-ICU clinics in Australia, with new clinics being planned in several states. As such, the findings of this study provide an opportunity to inform post-ICU care both locally and nationally.

Diverse research and clinical eﬀorts to improve the experience and outcomes of patients admitted to ICUs are ongoing within Metro North HHS. This study is complementary to those efforts and extends collaboration between the units, other directorates (mental health), across disciplines, and academic partners.

# Study plan / participants and recruitment

**Study design:**

This pilot study is a prospective, single site, parallel randomised controlled trial. Data will be collected with consent from routinely kept hospital records, and from participants at two times as specified below.

**Participants and sample calculation:**

Data will be collected from a sample of approximately 30 patients attending the Redcliffe ICU follow-up clinic over a 12-month period, with 15 randomised to the control and intervention arms respectively.

**PICS Feature Measure Minimally Clinically Important Difference (MCID)**

Anxiety/Depression HADS* ≥ 2.5 points[17]

PTSD PCL-5 ≥ 10 points[18]

Physical Function EQ5D* ≥ 0.5 points[19]

*Collected as part of routine clinic practices

**Inclusion criteria:**

People discharged from the participating ICU will be eligible to participate if they are:

- Meets the Post-ICU Clinic criteria
  - ICU admission >48hrs
  - Nil cognitive impairment that prevents participation
- Aged 18 years or over
- Residing in Australia
- Sufficiently fluent in English to complete recruitment and data collection processes
- Able to provide a GP with which the research team can correspond about the intervention
- Likely to be contactable at the 6-month follow-up time

**Exclusion criteria:**

- Patients whose life expectancy at discharge is estimated by their clinical team to be less than 6 months
- Unable or unwilling to provide consent to participate for the duration of the study
- Provide consent, but do not provide baseline or 6-month follow-up data
- Unlikely to remain contactable for 6 months after their clinic appointment

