Six months after clinic presentation, research staff will contact all participants to offer a follow-up appointment either in the clinic or by phone and conduct the follow-up survey as described below. Participants will be invited to continue and will have the opportunity to withdraw from the study before this additional data is collected.

At the 6-month follow-up timepoint when potential participants do not respond to the first contact attempt, research staff will attempt contact again one week later. Potential participants who remain uncontactable after the second attempt will be considered lost to follow-up and not contacted again.

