# Study procedure

Following verbal consent being provided, participants will be randomised to attend the clinic either when the psychiatrist is present or absent block randomisation in blocks of 4 or 6, in a 1:1 ratio, with the list generated by the study statistician (AB) and provided in enclosed envelopes to conceal allocation until verbal consent is provided. Full written consent will then be obtained when they attend their appointment.

Data will be collected with participant permission from their clinical records and medical history through a data request to ICU data collectors and hospital coders. These data will include demographics, frailty scores, diagnoses and severity of illness, previous mental health history, medications, multidisciplinary interventions, evidence of delirium during their admission and in-hospital complications.

| **Time points** | **Data collected** | |
| --- | --- | --- |
| Discharge from ICU | Contacted by clinical staff about the clinic. | |
| Clinic Appointment | Consent to participate, PICF completed. Routine Hospital Data accessed. Initial survey provided. Randomised to intervention or control arm. | |
|  | Control Group  Standard clinic cares provided as described below. | Intervention Group  Early psychiatric intervention provided as described below, in addition to standard clinic cares. |
| Intervention Follow-up |  | Participant contacted to evaluate response/tolerability of intervention. GP provided further advice as detailed below. |
| 6 Month Follow-up | Participant provides consent to continue participating and completes Follow-up Survey. | |

The timeframe of data collection is summarised in the table below:

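### An exclusion criterion that can be applied only six months after randomisation would, on its ordinary reading, remove randomised participants from the primary comparison

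*Protocol*

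**What the plan says.** The protocol's Exclusion criteria list people who "Provide consent, but do not provide baseline or 6-month follow-up data". A separate bullet in the same list excludes, prospectively, those not expected to stay reachable for six months, and the Inclusion criteria contain its mirror image.

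The sample is "approximately 30 patients attending the Redcliffe ICU follow-up clinic over a 12-month period", "with 15 randomised to the control and intervention arms respectively".

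The protocol describes the timing of randomisation in more than one way. The Study procedure text says "Following verbal consent being provided, participants will be randomised to attend the clinic either when the psychiatrist is present or absent". The time-point table in the same section puts "Randomised to intervention or control arm" at the clinic appointment. The Consent section speaks of randomising before consent. All of these come well before the 6-month contact.

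Two other sections deal with people who give no 6-month data. Sampling and recruitment says: "Potential participants who remain uncontactable after the second attempt will be considered lost to follow-up and not contacted again". Statistical analysis says: "The number of patients approached and consented will be tabulated, together with the number who dropped out or died".

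The primary outcome is the averaged Post Appointment Questionnaire, compared between arms by t-test (Statistical analysis). The Follow-up Survey section has participants repeat that questionnaire at six months, so it is first given earlier.

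**The concern.** An exclusion criterion should be decidable before allocation. This one depends on what a participant does about six months later, after the arms have been treated differently. Applied as written, it turns a participant who dies, drops out or cannot be reached into someone who should never have been in the trial.

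Two things are at stake. First, a person who answered the Post Appointment Questionnaire after the clinic visit and was later lost would have that answer set aside, although acceptability had been measured. The arms would then be compared on a subset selected after randomisation. If loss relates to how participants felt about the appointment, and differs by arm, the comparison is biased. Second, the denominator becomes inconsistent: the same person is excluded in one section and counted as a loss in another.

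**Working it through.** **Order of events**

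| Step | When | Source in protocol |
|---|---|---|
| Randomisation | At or before the clinic appointment | Study procedure (text and table); Consent |
| First Post Appointment Questionnaire | After the appointment (inferred from its name and its repetition at 6 months) | Post Appointment Questionnaire; Follow-up Survey |
| 6-month data given or not | About 6 months after the appointment | 6 Month Outcomes Follow-up |
| Exclusion for lack of 6-month data | Only after the step above | Exclusion criteria |

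On every account of randomisation, the exclusion follows allocation, treatment and the first primary-outcome response. The baseline half of the bullet may fall before or after allocation, depending on which account is followed; the point does not rest on it.

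**The same person in three sections.** Take someone who completes the questionnaire after the appointment and cannot be reached at six months. Under Exclusion criteria that person is excluded. Under Sampling and recruitment the person is lost to follow-up. Under Statistical analysis the person would be counted among those who dropped out or died. No passage says which label governs the analysis.

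**Sample size.** The only figure to reproduce is 15 + 15 = 30, which agrees. The protocol gives no dropout rate, so the loss rates below are assumptions.

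**Denominator**, with 30 randomised:

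| Assumed loss | Completers | Over all randomised (Wilson 95% CI) | Over those left by the bullet |
|---|---|---|---|
| 10% | 27 | 27/30 = 90% (74 to 97) | 27/27 |
| 20% | 24 | 24/30 = 80% (63 to 91) | 24/24 |
| 30% | 21 | 21/30 = 70% (52 to 83) | 21/21 |
| 40% | 18 | 18/30 = 60% (42 to 75) | 18/18 |

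**Bias in the primary comparison.** Assume standard normal scores in both arms and no true effect. One arm loses 3 of 15 and the other loses none, which is 3/30 = 10% overall. Dropout is driven by a variable with correlation r to the score, and the 3 participants lowest on that variable are removed. A two-sided 5% t-test then compares 12 with 15.

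If r = 1, the three lowest of 15 scores average about -1.31 SD, so removing them raises the arm mean by 3 × 1.31 / 12 = 0.33 SD. For smaller r the shift is r × 0.33.

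| r | Shift in mean | False rejection (simulated) |
|---|---|---|
| 0.3 | 0.10 SD | about 6% |
| 0.5 | 0.16 SD | about 7% |
| 1 (exactly the three lowest scorers) | 0.33 SD | about 16% |

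A second scenario lets both arms lose the same fraction p, with loss related to score in one arm only. The large-sample shift is r × φ(c)/(1 − p), where c is the normal quantile at 1 − p. For p from 10% to 40% this gives 0.06 to 0.19 SD at r = 0.3 and 0.10 to 0.32 SD at r = 0.5. If loss is unrelated to the score, the expected shift is zero and only numbers are lost.

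**The case against.** The strongest reply is that the bullet is a clumsy note about completers with limited effect. Several parts of that reply stand.

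- A reader might infer that retention becomes 100% by definition and can no longer be estimated. The documents do not support that. The last column of the denominator table follows only if the bullet is read alone. Sampling and recruitment still recognises loss to follow-up, and Statistical analysis still tabulates consents, drop-outs and deaths, so retention could be recovered. Retention is also not a named outcome: the primary objective specifies cost, practicability and acceptability.
- A reader might infer that the bullet damages every randomised comparison. For the 6-month ANCOVA it adds little, because people without 6-month data are missing from an observed-data analysis with or without it.
- The wording could mean lacking both baseline and 6-month data. Someone with baseline data only would then stay in. Lacking either is the ordinary reading, and an exclusion rule open to both still needs correcting.
- Tabulating drop-outs is compatible with a completers-only analysis, so that sentence does not settle who is analysed. The protocol names no analysis population, and one may be defined in an analysis plan not shown. That answers a charge of missing detail. It does not answer this point, because the protocol already fixes a rule, and a plan analysing everyone randomised would conflict with it.
- The 16% false rejection rate should not be taken as typical. It requires one-sided loss made up of exactly the lowest scorers, and nothing in the protocol indicates such a pattern.
- The two-attempt contact rule is a choice, not an error, and this point gives no reason to change it.

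**Conclusion.** The criterion is wrong as written. Its 6-month half cannot determine eligibility and, ordinarily read, operates as an exclusion after randomisation. It would set aside primary-outcome answers already given and is not aligned with the protocol's own treatment of losses.

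The damage is confined to the post-appointment primary comparison and the denominator. With 3 of 15 lost in one arm only, the bias is about 0.10 SD under a modest link between dropout and score, and 0.33 SD at the extreme. These figures rest on assumed loss and correlation. If loss is unrelated to the score, the cost is lost data and an unclear denominator, not bias. The conclusion also rests on the either-missing reading and on the questionnaire first being given soon after the appointment, which the protocol implies but does not timetable.

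**What to change.** 1. Delete the bullet. The prospective bullet on people unlikely to remain reachable already does the eligibility work.
2. State that all randomised participants are analysed in their allocated arm for every outcome they provided, with the primary outcome using everyone who has a post-appointment questionnaire.
3. Report non-completion and deaths by arm, with all those randomised as the denominator.
4. Align Exclusion criteria, Sampling and recruitment, and Statistical analysis, so that a person without 6-month data has one status throughout.

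The cost is a protocol amendment removing one bullet and adding a sentence or two on the analysis population and reporting. No extra data collection or change to the contact schedule is needed. The change should be made before outcomes are known, because a later decision on whom to keep would be hard to defend.
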